### Intervention

Participants in INTV take part in a standardized 12-week home-based training program. The program is specifically-tailored for geriatric patients with CI after post-ward rehabilitation to improve motor performance and enhance PA. The training intervention was derived from an exercise program developed by our research group, which was feasible and effective to increase strength and functional performances in patients with CI [24]. Based on results of a successfully conducted home-based exercise pilot RCT, our program includes six exercises to improve static and dynamic postural control (i.e., standing and walking) and strength (i.e., tiptoe stance, stair climbing, sit-to-stand transfers). Exercises are explained and regularly reviewed by a professional trainer and illustrated at the patient’s home using a large poster (84.1 × 59.4 cm; Fig. 2). A brief description of key elements for each exercise is provided using a printed manual. Training progress and adherence is supervised by weekly phone calls and regular home visits of the trainer (5 visits in 12 weeks).

**Fig. 2 Fig2:**
[figure not shown]
Illustration of the exercise provided on a poster and used in the intervention. The upper row displays balance exercise (**a**-**c**), the lower row represents strength exercises (**d**-**f**)

One major aim of the intervention is to motivate participants to induce behavioral changes in terms of enhanced PA by incorporating walking trails into their everyday life. Therefore, an individual outdoor walking course is defined next to the patients’ homes (i.e., in the respective neighborhoods). Motivational strategies will be used to encourage behavioral changes. Participants are asked to regularly set individual goals, e.g., to extend the individually-defined walking distance. Barriers hampering regular walking sessions and solutions to overcome these barriers are identified in cooperation with the trainer and benefits of regular training/walking sessions are discussed. Variations of the walking trails and physical exercises program are developed to adjust the training protocol to meet the participants’ needs (e.g., number of repetitions, handrail support, eyes open/closed, etc.). During the home visits and weekly phone calls, the trainer encourages the participant to conduct the training exercises and the walking trails independently. Furthermore, training descriptions (i.e., training manual; poster), training logs and pedometers are provided to foster participation, to enable self-monitoring of performance, and to define individual goals (e.g., increase number of daily steps). Participation in a local sports club is offered to each participant as an incentive for social participation.

The training program will include a motivational concept that is based on the Theory of Planned Behavior (TPB [50]), Social-Cognitive Theory (SCogT [51]), and Control Theory (CT [52]). The concept will use behavioral change techniques introduced by Abraham & Michie (cf. [53] for a detailed description of the theoretical framework) and integrated into our intervention as followed:Information about benefits/consequences of regular training and walking sessions are provided (based on TPB);Encouragement to change daily routines (i.e., integrate training, walk regularly, join a local sport club) (based on TPB);Barrier identification that hamper training and development of solutions to overcome barriers (based on SCogT);Set graded tasks (i.e., variations of exercises and walking trails are developed) (based on SCogT);Provide specific instructions (during home visits using poster and manuals) (based on SCogT);Definition of training goals (i.e., frequency, intensity and duration of exercises and walking trails) (based on CT);Review of behavioral goals (home visits, regular phone calls, pedometer) (based on CT);Self-monitoring of behavior (training logs, pedometer) (based on CT);Provide feedback to reinforce behavioral change (home visits, phone calls, pedometer) (based on CT/positive).

These behavioral change techniques are used to encourage patients to translate their intentions into behavioral change. Participants are expected to develop intrinsic motivation and volition to adapt their behavior.

Participants in CTRL receive newsletter-based information about unspecific flexibility and strength training, nutrition and relaxation over a period of 12 weeks. Similar to INTV, participants are called weekly and receive the same amount of home visits as the INTV group to exclude bias effects based on social support. After finishing the project, participants in CTRL will have the opportunity to perform the same exercise program than INTV and also join the local sports club.

### Statistical analysis and sample size

An intention to treat analysis will be conducted. We performed an a priori power analysis to determine the sample size necessary to obtain significant effects in PA. Power analysis for PA is difficult to calculate since studies using identical sensor-based physical activity assessments in cognitively-impaired geriatric patients have not been available. Thus, the effect size is based on a study conducting a functional strength training program in 137 institutionalized patients [54]. PA, as assessed by the MTI Actigraph, showed an average increase of PA by 43% in the strength training group compared to a control group (effect size: eta^2^ = 0.18). A priori power analysis was performed using GPower 3.1 software [55]. A repeated measure analysis of co-variance (ANCOVA) design including two groups and two repeated measurements yielded a total sample size of *N* = 101 (α = 0.05; critical F = 2.69). Estimating a drop out of 15%, we will recruit a total of 116 participants. For motor performance, as assessed by the SPPB total score, a pilot study conducted by our research group showed that performance improvements can be achieved using relatively small sample sizes (*N* = 34; large effect size: eta^2^ = 0.22 [56]). Repeated measures ANCOVA will be used to determine effects of the home-based training program on primary and secondary outcomes for effects of intervention (T1-T2) and sustainability of effects (T1-T3). Effect sizes are determined by calculating eta^2^ [57]. All data will be analyzed using SPSS 23.0 (SPSS Inc., Chicago, Ill., USA).

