### Measures

After inclusion of the participants, primary and secondary outcome parameters are registered at baseline (T1), following the training intervention (T2), and 12 weeks after the training is completed (T3). At baseline, additional descriptive parameters (i.e., age, gender, height, weight, Barthel Index) are registered. Blinded assessors will conduct the measurements at the patients’ home.

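### Intention to treat is promised with 15% drop-out expected, but the only named method uses complete T1-T2 or T1-T3 pairs; one mixed model on all randomised patients would serve the promise better

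*Protocol article*

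**What the plan says.** All the relevant statements stand in the protocol article, section Statistical analysis and sample size.

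- Principle: "An intention to treat analysis will be conducted".
- Expected loss and the response to it: "Estimating a drop out of 15%, we will recruit a total of 116 participants".
- Method: repeated measures ANCOVA, the only model named, is to be applied to "primary and secondary outcomes for effects of intervention (T1-T2) and sustainability of effects (T1-T3".
- Sample size basis: a "design including two groups and two repeated measurements yielded a total sample size of" 101, so each planned test is a comparison of two visits.
- Software: "All data will be analyzed using SPSS 23.0". No procedure within it is named.

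The section Measures sets three visits: T1 at baseline, T2 after training, and T3 twelve weeks after training ends. The article does not define intention to treat, does not mention imputation or a mixed model, and does not say that patients who drop out are excluded.

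**The concern.** Classical repeated measures ANCOVA needs a value at each level of the repeated factor. Run on observed data for two visits, it can use only patients who have both. The article therefore promises an analysis of everyone randomised, but the method it names does not by itself include patients without the second measurement. Its only answer to drop-out is to recruit more, which treats those who leave as lost to the analysis.

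With separate pairs, the T1-T3 test also makes no use of T2. For a patient seen at T2 and lost afterwards, T2 is the most recent information about where that patient was heading.

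What is at stake is selective loss. The Background describes frail, multi-morbid patients with raised institutionalisation and mortality, apathy, and worse adherence to home training in those with cognitive impairment. The arms also ask different things of patients: exercises, walking trails and goal setting in one, newsletter information in the other. Loss related to function, and different between arms, is plausible, though the documents do not show that it will occur.

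**Working it through.** **1. The plan's own figure.** Inputs from Statistical analysis and sample size: required N = 101, loss 15%. 101 x 1.15 = 116.15, which gives the stated 116.

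**2. Patients analysed.** Assume the 15% applies to the contrast in question and no values are imputed.
- Analysed: 116 x 0.85 = 98.6.
- Left out: 116 x 0.15 = 17.4, about 17 randomised patients.
- To keep 101 complete pairs: 101 / 0.85 = 118.8, so 119 would be needed.

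**3. Power is not the issue.** With eta² = 0.18, f = √(0.18/0.82) = 0.469. At alpha 0.05, power with 98 to 99 patients against 116 is about 0.996 against 0.999 (numerator df 1). With numerator df 3, which the stated critical F implies, it is about 0.98 against 0.992.

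**4. Possible bias (illustration; none of these inputs is in the documents).** Assume no true effect, outcomes in SD units, correlations T1-T2 0.5, T2-T3 0.7 and T1-T3 0.5. Loss is 15%, in one arm only, with log-odds of leaving rising by 1 per SD of lower function. Those who stay then average 0.133 SD higher on the variable that drives loss.

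*T2, loss depends on T1:*
- Unadjusted change: 0.133 x (0.5 - 1) = -0.066.
- T1 as covariate (slope 0.5): 0.133 x 0.5 - 0.5 x 0.133 = 0.
- Extreme case, lowest 15% leave: shift 0.274, unadjusted change 0.274 x (-0.5) = -0.137. It is again zero with T1 as covariate.

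*T3, loss depends on T2:*
- The T3 mean shifts by 0.133 x 0.7 = 0.093, but T1 shifts too, by 0.133 x 0.5 = 0.066.
- Unadjusted change: 0.133 x (0.7 - 0.5) = +0.027.
- T1 as covariate: 0.093 - 0.5 x 0.066 = +0.060.

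Simulation with 4 million draws per arm agrees for the logistic cases: -0.066 and 0.001 at T2, +0.027 and +0.061 at T3. With the same loss mechanism in both arms, all four contrasts are within 0.001 of zero.

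**5. Scale.** With a change-score SD of 1, which these correlations imply, the difference detectable with 80% power in about 99 patients is roughly 0.57 SD. On that scale the change-score biases in the logistic cases are 0.066/0.57 = 12% at T2 and 0.027/0.57 = 5% at T3.

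**The case against.** The strongest reply is that the article never says it will analyse completers. It names software, not a procedure, and SPSS can impute or fit a mixed model. Intention to treat can also mean analysis in the allocated arm regardless of adherence, which ANCOVA permits. Missing-data rules commonly sit in a full protocol or analysis plan that is not shown. All of this stands, and it rules out several stronger readings.

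- *A reader might infer that the plan is a completers analysis that contradicts intention to treat.* The text does not say so. That reading holds only if the named method is run on observed data without imputation.
- *A reader might infer that every patient with a missing visit is dropped.* Exclusion is per contrast. A patient missing only T3 stays in T1-T2, and one missing only T2 stays in T1-T3.
- *A reader might infer that the sustainability contrast suffers most.* The illustration does not establish this: the order of T2 and T3 depends on whether T1 is the covariate, and the article does not name the covariate. The 0.093 shift in the raw T3 mean belongs to neither planned analysis.

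It is also fair to say that one-arm loss is the unfavourable case. Under Intervention, both arms get the same weekly calls and number of home visits, which weighs somewhat against strongly arm-specific loss.

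The reply does not remove the point. The article fixes a principle, a loss rate, a response to loss and a method. The method as described leaves out patients whom the principle is meant to keep, and it discards T2 from the T1-T3 test.

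**Conclusion.** The point holds in a limited form. As described, the named method uses complete pairs, so about 17 of 116 randomised patients would be missing from a contrast at the expected 15% loss, and the T1-T3 test would ignore the T2 values of patients lost later. Recruiting 116 restores numbers, not comparability.

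The size of any bias cannot be read from the documents. Under one-arm loss and the assumed correlations it is modest, up to about 0.07 SD with logistic loss, and it vanishes at T2 if T1 is the covariate or in both contrasts if the arms lose patients alike. The count of 17 assumes that no imputation is done and that the 15% applies to the contrast. This is a cheap improvement to the stated method, not a demonstrated error in the trial's result.

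**What to change.** Make the primary analysis one linear mixed model for repeated measures (SPSS MIXED, REML, unstructured covariance):
- all randomised patients, as allocated;
- T1, T2 and T3 modelled together as outcomes, with a baseline mean common to both arms;
- group contrasts at T2 (effect of intervention) and T3 (sustainability).

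State that patients with any measured visit contribute, and keep the complete-pair ANCOVA for T1-T2 and T1-T3 as a sensitivity analysis, naming its covariate.

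The cost is a few sentences and a different procedure in the same software. The downside is that the model relies on data being missing at random given the observed visits. That should be stated.

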## Methods/Design

### Study design

The presented study is a blinded randomized-controlled trial (RCT) with two arms (i.e., an intervention group [INTV] and a control group [CTRL]; Fig. 1) and will be implemented according to CONSORT guidelines [32]. Ethical approval according to the ethical standards of the Helsinki declaration was obtained from the internal review board at the Medical Faculty of the University of Heidelberg, Germany (reference#: S-252/2015). The study protocol has been registered with the “International Standard Randomized Controlled Trial Number” (ISRCTN) trial register (http://www.isrctn.com/ISRCTN82378327).

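### The printed critical F of 2.69 does not fit a two-group, two-measurement test, and N = 101 does not follow from eta² = 0.18 at conventional power

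*Protocol article*

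**What the plan says.** All of the relevant figures stand in one paragraph of the protocol article, under Statistical analysis and sample size.

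- The planning effect for physical activity is borrowed from a strength training study in 137 institutionalized patients ("effect size: eta^2^ = 0.18").
- The tool is named: "A priori power analysis was performed using GPower 3.1 software".
- The powered model is a repeated measures ANCOVA, "including two groups and two repeated measurements yielded a total sample size of" 101, reported with "α = 0.05; critical F = 2.69".
- Recruitment builds on that number: "Estimating a drop out of 15%, we will recruit a total of 116 participants".
- The planned analyses are repeated measures ANCOVAs "for effects of intervention (T1-T2) and sustainability of effects (T1-T3"), so each uses two time points.

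The Study design section confirms a "blinded randomized-controlled trial (RCT) with two arms". The article does not state the power, the numerator degrees of freedom, the number of covariates or the correlation between measurements.

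**The concern.** A critical F is fixed by alpha and the two degrees of freedom. It does not depend on the effect size, and once N is given it does not depend on the power. The printed value can therefore be checked against the printed design almost without assumptions, and it fails the check: it is far below anything that a 1-df test at 5% can produce.

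This is the article's only formal sample size calculation. For the SPPB it refers only to a pilot study. A reader will take 101 as the number needed to detect eta² = 0.18, and may read a null physical activity result in that light. If the calculation was run for a test other than the one described, that reading is wrong and the sensitivity of the trial is misdescribed. This matters more because the article itself says that no study with an identical sensor-based measure in this population was available to plan from.

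**Working it through.** **Inputs.** From the article: alpha = 0.05, eta² = 0.18, two groups, two measurements, N = 101, critical F = 2.69. Not given, so varied: power 80 to 99%; 0 or 1 covariate; correlation ρ between measurements.

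**Step 1: the printed critical F.** Numerator df in a 2 × 2 design:

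- group: 2 − 1 = 1
- time: 2 − 1 = 1
- group by time: (2 − 1)(2 − 1) = 1

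Upper 5% points of F near N = 101:

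| Numerator df | Denominator df | Critical F |
|---|---|---|
| 1 | 98 | 3.938 |
| 1 | 99 | 3.937 |
| 2 | 98 | 3.09 |
| 3 | 97 | 2.698 |
| 3 | 96 | 2.699 |

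On 1 numerator df the 5% value falls towards 3.84 as N grows and never goes below it. No choice of power, ρ or covariates gives 2.69. Only 3 df comes close, and then 2.69 is a truncation, because 2.698 rounds to 2.70. A change of alpha does not explain it: on 1 and 98 df, F = 2.69 has an upper tail of 0.104, while alpha = 0.10 would give a critical F of 2.76.

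**Step 2: the printed N.** Convert the effect:

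f² = eta² / (1 − eta²) = 0.18 / 0.82 = 0.2195, so f = 0.4685.

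For an ANCOVA the noncentrality is λ = f² × N, with denominator df = N − groups − covariates. The smallest N that reaches each power is:

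| Calculation | 80% | 90% | 95% | 99% |
|---|---|---|---|---|
| 1 df, f² = 0.2195 | 38 | 50 | 62 | 86 |
| 3 df, f² = 0.2195 | 54 | 69 | 83 | 112 |
| 3 df, f² = 0.18 (eta² not converted) | 65 | 83 | 100 | 135 |

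As a group-by-time interaction in a repeated measures ANOVA, λ = f² × N × 2 / (1 − ρ). The need is then 20 to 44 patients at ρ = 0 and 12 to 24 at ρ = 0.5, over the same range of power. No 1-df variant at 80 to 99% power gives 101.

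**Step 3: power at N = 101.** For the 1-df ANCOVA, λ = 0.2195 × 101 = 22.2 with 98 denominator df. Power is 0.997.

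**Step 4: where the figures might come from.** The nearest match to both printed numbers is the last row of the table at 95% power: N = 100 with critical F about 2.70. Exactly 101 needs f of about 0.421, against √0.18 = 0.424. This is a guess at the origin, and it misses both printed figures slightly.

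**Step 5: what the sample can detect.** After 15% dropout, 116 × 0.85 = 98.6, or about 98 evaluable patients. With 1 df and one covariate, 80% power needs λ of about 8.01:

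- f² = 8.01 / 98 = 0.0817
- partial eta² = 0.0817 / 1.0817 = 0.076
- d = 2f = 2 × √0.0817 = 0.57, in units of the covariate-adjusted residual SD

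**The case against.** The strongest reply is that nothing in the trial changes. For eta² = 0.18 on 1 df, 101 patients are more than enough, and patients, endpoints and model stay as they are. That stands. This is an error in reporting and traceability, and it does not make the trial too small.

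Second, the article states no power, so N = 101 taken alone cannot be shown to contradict eta² = 0.18: a 1-df ANCOVA at about 99.7% power would give it. That also stands, and the point on N is limited to conventional power for this reason. It does not rescue the critical F, which at N = 101 does not depend on power. Nor is this a complaint about detail left to a fuller document: the article prints both a design and a critical value, and no unseen document can make them agree.

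A reader might infer three stronger things, none of which the article supports.

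- *That 2.69 will serve as the significance threshold, so that type I error rises to about 10%.* The figure appears only as output of the power analysis. The analyses will be run in SPSS, and nothing says that 2.69 will be the cut-off there.
- *That the calculation was demonstrably run on 3 df with an unconverted effect size.* That route fits approximately but is unconfirmed.
- *That the article names a group-by-time test and powers something else.* It names only a repeated measures ANCOVA. The argument does not need the name, because every such effect in the stated design has 1 df.

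**Conclusion.** The point holds as an internal inconsistency in the stated basis of the sample size. The critical F of 2.69 is incompatible with two groups, two measurements and alpha = 0.05; the value at N = 101 is about 3.94. This rests on no assumption beyond the printed design. That N = 101 does not follow from eta² = 0.18 rests on two assumptions: power between 80 and 99%, and eta² converted in the usual way.

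The practical consequence is limited. The trial is not underpowered for its planning effect. What is lost is a traceable justification for 101, and so for 116, and a correct account of what the sample can detect. The correction is worth making but does not threaten the conduct of the trial.

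**What to change.** Rewrite the sample size paragraph:

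1. Rerun the calculation for the 1-df group contrast that will be tested, entering eta² = 0.18 as f = 0.4685.
2. Replace the critical F with about 3.94 and give the numerator df as 1.
3. State the power used, with the number of covariates or the correlation if the chosen procedure needs them.
4. Keep the recruitment target and say plainly that N exceeds the requirement for eta² = 0.18.
5. Optionally, add the sensitivity of the retained sample: about 98 evaluable patients give 80% power for a partial eta² of about 0.076, with d labelled as being in covariate-adjusted residual SD units. This supplements the literature-based planning effect and does not replace it.

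The cost is one paragraph and a short rerun in the software already named. Recruitment, endpoints and the analysis model do not change.

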**Methods:**

A sample of 101 geriatric patients with mild to moderate stage CI following ward-based rehabilitation will be recruited for a blinded, randomized controlled trial with two arms. The intervention group will conduct a 12 week home-based training, consisting of (1) Exercises to improve strength/power, and postural control; (2) Individual walking trails to enhance physical activity; (3) Implementation of patient-specific motivational strategies to promote behavioral changes. The control group will conduct 12 weeks of unspecific flexibility exercise. Both groups will complete a baseline measurement before starting the program, at the end of the intervention, and after 24 weeks for follow-up. Sensor-based as well as questionnaire-based measures will be applied to comprehensively assess intervention effects. Primary outcomes document motor performance, assessed by the Short Physical Performance Battery, and level of physical activity (PA), as assessed by duration of active episodes (i.e., sum of standing and walking). Secondary outcomes include various medical, psycho-social, various PA and motor outcomes, including sensor-based assessment as well as cost effectiveness.

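### The article gives two recruitment totals, 101 and 116, and 116 does not quite leave 101 patients after the 15% drop-out it is meant to cover

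*Protocol article*

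**What the plan says.** Two places in the protocol article give a number to recruit.

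- **Abstract, Methods:** "A sample of 101 geriatric patients with mild to moderate stage CI following ward-based rehabilitation will be recruited". No drop-out allowance is mentioned there.
- **Statistical analysis and sample size:** the power calculation "yielded a total sample size of *N* = 101", and the next sentence reads "Estimating a drop out of 15%, we will recruit a total of 116 participants".

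The calculation is described as a repeated-measures ANCOVA "design including two groups and two repeated measurements", with "α = 0.05; critical F = 2.69" and an assumed "effect size: eta^2^ = 0.18". The power it was run for is not given. The same section states that the analysis will be by intention to treat.

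**The concern.** A trial needs one figure at which enrolment is complete. Here the abstract and the sample-size section attach different figures to the same act of recruiting, and nothing in the abstract marks its 101 as the number analysed or completing. A reader who sees only the abstract takes away a target 15 patients below the one the sample-size section sets.

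The second problem lies within the sample-size section. The purpose of recruiting more than 101 is to have 101 left after losses. Drop-out is a share of those recruited, so the allowance should divide by the proportion retained. Adding 15% to the required number gives a total that falls slightly short at the very rate assumed. The stated inputs and the stated total therefore do not fit each other.

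**Working it through.** **Inputs, all from Statistical analysis and sample size unless noted**

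- Required number from the power analysis: 101
- Assumed drop-out: 15%
- Recruitment total: 116
- Recruitment figure in the abstract: 101
- Alpha 0.05, critical F 2.69, eta² 0.18
- Power: not stated

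**1. Reproduce the plan's 116.** 101 × (1 + 0.15) = 116.15, rounded to 116. So the drop-out rate was added to the required number.

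**2. Check what 116 leaves.** 116 × (1 − 0.15) = 98.6, that is 98 to 99 patients, 2 to 3 below 101.

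**3. Number needed to keep 101.** 101 / (1 − 0.15) = 118.8, rounded up to 119. Check: 119 × 0.85 = 101.2, whereas 118 × 0.85 = 100.3. The gap is 119 − 116 = 3 recruits.

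**4. Drop-out that 116 can absorb.** 1 − 101/116 = 0.129, or 12.9%, below the 15% assumed.

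**5. The two recruitment figures.** 116 − 101 = 15. If the abstract's 101 were taken literally as the enrolment total, 101 × 0.85 = 85.9 patients would remain.

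**6. What the slip in step 2 costs in power.** Since power is not stated, I assume in turn that 101 patients give exactly 80%, 90% or 95%. For each I solve for the effect that does so in a fixed-effects ANCOVA F test with one covariate, then recompute power at 98 and 99 with that effect held fixed. I use 1 numerator degree of freedom (a plain two-group comparison) and 3. The second is included because the stated critical F of 2.69 is close to the 3-df value near N = 101 (about 2.70) and far from the 1-df value (about 3.94).

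| Assumed power at 101 | Numerator df | Power at 99 | Power at 98 |
|---|---|---|---|
| 80% | 1 | 79.2% | 78.8% |
| 80% | 3 | 79.1% | 78.6% |
| 90% | 1 | 89.4% | 89.1% |
| 90% | 3 | 89.3% | 89.0% |
| 95% | 1 | 94.6% | 94.4% |
| 95% | 3 | 94.6% | 94.3% |

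The loss runs from 0.4 points (95% to 94.6%) to 1.4 points (80% to 78.6%).

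**7. The same check at the plan's own effect.** eta² = 0.18 gives f² = 0.18/0.82 and f = 0.469. In this F test, power at 101 and 98 is 99.7% and 99.6% (1 df), or 98.2% and 97.9% (3 df). The change is negligible.

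**The case against.** **The abstract's 101 is plainly the pre-inflation number.** This is probably right. It is the same 101 that the sample-size section reports, so it is not a further independent figure, and that section gives an explicit target with its derivation. What stands is that the abstract says recruited. Nor does 101 match the number expected after drop-out, which is 98.6.

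**Intention to treat makes drop-out irrelevant.** The article does not call 101 an evaluable number, and how patients who drop out enter the analysis may be set out in a plan not shown. But the sample-size section itself enlarges the total for drop-out, so it treats 101 as the number wanted after losses. Its figure should meet that premise.

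**Three recruits do not matter.** Correct as to consequence. A reader might infer that the trial is underpowered because 116 is too few. The documents do not support that: the loss is about a percentage point, and at the planning effect it is negligible. A reader might also infer that the trial will stop at 101 recruits and end with about 86 patients. That would follow only if the abstract overrode the sample-size section, and nothing in the article suggests it does.

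**A detectable difference could be quoted to show the size.** It would need an assumed power and an assumed test. A 1-df test does not match the stated critical F, so such figures would not be the article's own. I leave them out.

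**Conclusion.** Both inconsistencies are real and follow from the printed figures alone. The weightier one is the pair of recruitment totals, 101 in the abstract and 116 in the sample-size section. The lesser one is the allowance: 116 leaves 98 to 99 patients at 15% drop-out, and 119 would be needed for 101.

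The shortfall of 3 recruits involves no assumption beyond reading drop-out as a share of those recruited. The power loss of 0.4 to 1.4 points does rest on assumptions: that 101 patients give 80% to 95% power, that the test is an ANCOVA F test with 1 or 3 numerator degrees of freedom, and that patients who drop out contribute nothing to the analysis. Whether 101 is itself well founded is a separate question on which this point takes no position.

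Grade: a should-fix correction of minor weight. The design and the trial's ability to answer its question are not affected.

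**What to change.** 1. In the abstract, replace 101 with the recruitment figure from the sample-size section, so that one total appears throughout. If 101 is kept there, label it as the number required by the power analysis.
2. In Statistical analysis and sample size, either
   - keep 116 and state that about 98 patients are expected after 15% drop-out, with the power restated at that number; or
   - if 101 after drop-out is binding, change the target to 119 here and in the abstract.

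The first option changes wording only, plus one power figure that will be very slightly less favourable. The second adds 3 recruits. Neither touches the endpoints, the intervention or the analysis method.

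### The planned repeated measures ANCOVA names neither its covariate nor the treatment test; on its natural reading it is a change-score analysis, less precise than adjusting T2 and T3 for the T1 value

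*Protocol article*

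**What the plan says.** In the protocol article, the section on statistical analysis and sample size gives the method for all outcomes: "Repeated measures ANCOVA will be used to determine effects of the home-based training program on primary and secondary outcomes", and the comparisons: "for effects of intervention (T1-T2) and sustainability of effects (T1-T3". The sample size was worked out for the same layout: "A repeated measure analysis of co-variance (ANCOVA) design including two groups and two repeated measurements".

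The Measures section defines the time points. Outcomes "are registered at baseline (T1), following the training intervention (T2), and 12 weeks after the training is completed (T3". Each of the two comparisons therefore contains exactly two time points, one of which is the baseline.

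The method is called analysis of covariance, but no covariate is named anywhere in the article. Nor does the text say which term of the model is the test of treatment. The only summary of effect that it mentions is eta².

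**The concern.** If T1 and T2 are the two levels of the repeated factor, baseline is part of the outcome. The group-by-time test then compares mean change between the arms, which amounts to fixing the baseline slope at 1. When T1 and T2 are less than perfectly correlated, that slope is too steep, and the noise in T1 is carried into the treatment estimate.

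The same model also yields a group main effect. That term compares the average of T1 and T2 between arms, so with no effect possible at T1 it estimates only half of the effect at T2.

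At stake is precision on both primary outcomes, the SPPB total score and the duration of active episodes, and some freedom over which term is reported. Physical activity rests on a 48-hour recording, and the article itself says that power for it is hard to calculate. That is a poor position from which to give precision away.

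**Working it through.** **Does the plan's own sample size reveal the model?** It does not. The article gives N = 101, with "α = 0.05; critical F = 2.69" and "effect size: eta^2^ = 0.18"; power is not stated.
- f = sqrt(0.18/0.82) = 0.4685.
- With two groups and two times, both the group and the group-by-time tests have 1 numerator df. The critical F at N = 101 is then about 3.94, not 2.69. A value near 2.70 belongs to 3 numerator df: F(3, 97) = 2.698.
- ANCOVA with 1 numerator df and f = 0.4685 needs N = 38, 50, 62 or 86 for 80, 90, 95 or 99% power.

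N = 101 was therefore not reproduced from the stated inputs, and the calculation cannot settle which term or covariate was meant. Why it does not reproduce is a separate matter.

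**The algebra.** Assume equal variance sigma² at T1 and T2, correlation rho and 1:1 allocation (the ratio is not stated).
- Change score: variance 2·sigma²·(1−rho).
- T2 adjusted for T1: variance sigma²·(1−rho²).
- Ratio: (1−rho²) / [2(1−rho)] = (1+rho)/2.

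**Checks.** On one simulated data set, the group-by-time F and the squared t on change were both 7.424. With T1 added as covariate, the model for change and the model for T2 gave the same treatment estimate (0.456) and the same t (2.760). In 4,000 simulated trials per rho at N = 101, the variance ratios were 0.69, 0.76, 0.86 and 0.96 for rho = 0.3, 0.5, 0.7 and 0.9.

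**Size at N = 101**, supposing that the change-score analysis has 80% power:

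| assumed rho | variance ratio | power with T1 as covariate | N for the same 80% |
|---|---|---|---|
| 0.3 | 0.65 | 93% | 68 |
| 0.5 | 0.75 | 90% | 78 |
| 0.7 | 0.85 | 86% | 88 |
| 0.9 | 0.95 | 82% | 98 |

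**Power at given effects**, with 98 evaluable (116 × 0.85 = 98.6), two-sided alpha 0.05, noncentral t, SE = sqrt(4v/98), with v = 2(1−rho) for change and 1−rho² for T1 as covariate. The value d = 0.5 is an assumption. The value d = 2f = 0.94 comes from eta² = 0.18 read as a between-group effect, which is also an assumption.

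| assumed rho | d = 0.5: change / covariate | d = 0.94: change / covariate |
|---|---|---|
| 0.3 | 0.54 / 0.73 | 0.973 / 0.998 |
| 0.5 | 0.69 / 0.81 | 0.996 / 0.9996 |
| 0.7 | 0.89 / 0.93 | both above 0.999 |

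For the SPPB pilot effect, eta² = 0.22 (d about 1.06), power at rho = 0.3 is 0.993 against 0.9998.

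If the group main effect without a T1 covariate were read as the treatment test, the effect would be d/2 with variance sigma²(1+rho)/2. At d = 0.5 and rho = 0.5, power would be about 0.29.

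**Cost of the covariate.** One residual df, and a finite-sample factor of 1 + 1/(N−4) = 98/97 at N = 101. Setting (98/97)(1+rho)/2 = 1 gives rho of about 0.98, so the gain disappears only above that.

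**The case against.** The strongest reply is that the article says ANCOVA twice, and an ANCOVA has a covariate. If that covariate is T1, the plan already is the better analysis: as the check shows, a T1-T2 model with T1 as covariate returns the same estimate and t as T2 adjusted for T1. The labels T1-T2 and T1-T3 may also just name periods, and a condensed article can leave the covariate list to a fuller document. This stands to the extent that a reader might infer that the plan is stated to be a change-score analysis, or that T1 is no longer available as a covariate. The text supports neither. The change-score reading is the natural one, since T1 is counted as a repeated measurement, but it is not written down. If the unnamed covariate were something else, such as age, the baseline slope would still be fixed at 1.

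A reader might also infer bias from chance baseline imbalance or regression to the mean. That does not follow: both estimators are unbiased under randomisation, and the difference is one of variance.

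Finally, the gain is small at the article's own planning effects, and no T1-T2 correlation is given. Both points are right and limit the practical size. They do not touch the variance ratio, which holds at any effect size, and the article itself says that the physical activity effect was borrowed from a study with a different population and a different assessment.

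**Conclusion.** The point holds as one of precision and of an incompletely fixed primary analysis, not of validity. The article commits to a method and to its comparisons, but leaves open the two things that decide what is tested: the covariate and the term. On the natural reading, the adjusted analysis would have 65 to 95% of the change-score variance for rho from 0.3 to 0.9.

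In power this runs from 19 points (d = 0.5, rho = 0.3) to next to nothing when rho is high or the planned large effects are real. These figures assume equal variances at T1 and T2, 1:1 allocation, and values of rho and d = 0.5 that are not in the documents. That a 48-hour recording or an SPPB score correlates only moderately over 12 weeks is plausible, but the documents do not show it.

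**What to change.** State that, for each primary outcome, the T2 value is compared between groups in a linear model with group as factor and the T1 value of the same outcome as covariate, and that the group term is the test of treatment. Use the same model with T3 in place of T2 for sustainability, and for secondary outcomes that have a T1 value. A longitudinal model with the baseline mean constrained to be equal across arms would serve as well. Report the adjusted mean difference with its 95% CI alongside eta².

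The cost is a sentence or two of wording and one residual degree of freedom. Both primary outcomes are already measured at T1, and the software named in the article fits the model directly. If T1 was the intended covariate all along, the sentence simply records it.
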